**LIST OF ABBREVIATIONS AND RELEVANT DEFINITIONS**

|                |                                                                                                                                                                                                                                                                                                                                                  |
|----------------|--------------------------------------------------------------------------------------------------------------------------------------------------------------------------------------------------------------------------------------------------------------------------------------------------------------------------------------------------|
| ABR     | ABR form (General Assessment and Registration form) is the application form that is required for submission to the accredited Ethics Committee (ABR = Algemene Beoordeling en Registratie)                                                                                                                                                |
| AE      | Adverse Event                                                                                                                                                                                                                                                                                                                             |
| AR      | Adverse Reaction                                                                                                                                                                                                                                                                                                                          |
| CA      | Competent Authority                                                                                                                                                                                                                                                                                                                       |
| CCMO    | Central Committee on Research Involving Human Subjects                                                                                                                                                                                                                                                                                    |
| CV      | Curriculum Vitae                                                                                                                                                                                                                                                                                                                          |
| DSMB    | Data Safety Monitoring Board                                                                                                                                                                                                                                                                                                              |
| EU      | European Union                                                                                                                                                                                                                                                                                                                            |
| EudraCT | European drug regulatory affairs Clinical Trials GCP Good Clinical Practice                                                                                                                                                                                                                                                               |
| IB      | Investigator's Brochure                                                                                                                                                                                                                                                                                                                   |
| IC      | Informed Consent                                                                                                                                                                                                                                                                                                                          |
| IMP     | Investigational Medicinal Product                                                                                                                                                                                                                                                                                                         |
| IMPD    | Investigational Medicinal Product Dossier                                                                                                                                                                                                                                                                                                 |
| METC    | Medical research ethics committee (MREC); in Dutch: medisch ethische toetsing commissie (METC)                                                                                                                                                                                                                                            |
| (S)AE   | Serious Adverse Event                                                                                                                                                                                                                                                                                                                     |
| SPC     | Summary of Product Characteristics (in Dutch: officiële productinformatie IB1-tekst)                                                                                                                                                                                                                                                      |
| Sponsor | The sponsor is the party that commissions the organisation or performance of the research, for example a pharmaceutical company, academic hospital, scientific organisation or investigator. A party that provides funding for a study but does not commission it is not regarded as the sponsor, but referred to as a subsidising party. |
| SUSAR   | Suspected Unexpected Serious Adverse Reaction                                                                                                                                                                                                                                                                                             |
| Wbp     | Personal Data Protection Act (in Dutch: Wet Bescherming Persoonsgegevens)                                                                                                                                                                                                                                                                 |
| WMO     | Medical Research Involving Human Subjects Act (Wet Medisch-wetenschappelijk Onderzoek met Mensen)                                                                                                                                                                                                                                         |

## SUMMARY

### Rationale:

Worldwide, approximately 400 million people are chronically infected with hepatitis B virus (HBV). Chronic HBV infection increases the risk of developing cirrhosis, hepatic decompensation and hepatocellular carcinoma (HCC).(1, 2) The risk of developing hepatocellular carcinoma is highest in HBeAg positive patients with high HBV DNA levels, but still the relative risk remains 10 for HBeAg negative patients. (3) Furthermore it has been shown that when HBsAg is cleared before cirrhosis has developed, the prognosis is excellent (4, 5). Recently we have shown that HBeAg negative patients with high HBV-DNA load and low baseline HBsAg levels had a significantly higher HBsAg clearance (positive predictive value of 85%) after combination therapy with peginterferon alfa2a (Peg-IFN) and adefovir. (6) Based on these results, a trial was designed to investigate whether combination of a nucleos(t)ide analogue combined with PegIFN, could also provoke a high rate of HBsAg clearance in chronic hepatitis B patients with low (HBV DNA <20,000 IU/mL) viral load.

### Study design:

This is a three arm open-label prospective randomized controlled trial. 150 patients will be enrolled into the study after assessment of eligibility. All patients must have documented HBsAg positivity for longer than 6 months, HBeAg negativity, anti-HBe positivity, HBV DNA < 20,000 IU/mL and ALT < 5 \* upper limit of normal. Patients with a Child Pugh class B or C will be excluded. Group 1 will consist of patients treated with Peg-IFN and adefovir, group 2 will consist of patients treated with Peg-IFN and tenofovir and group 3 will consist of untreated controls. Patients in group 1 and 2 will receive medication for the period of one year. For enrolment into the study a liverbiopsy at time of enrolment is compulsory and is advisable at end of treatment (week 48).

**Study population:** The study population will consist of 150 patients chronically infected with hepatitis B virus with low viral load and HBeAg negativity.

### Main study parameters/endpoints:

The aim of this study is to investigate what proportion of HBeAg negative, inactive carriers of the hepatitis B virus with low (< 20,000 IU/mL) load will lose HBsAg when treated with nucleot(s)ide analogue/Peg-IFN combination therapy.

**Nature and extent of the burden and risks associated with participation, benefit and group relatedness:**

During a period of 1.5 year blood samples will be collected and tested at 21 defined timepoints, the number of site visits will be 21 (see appendix table 1).

Questionnaires about compliance and quality of life will be asked to be filled in. Potential physical and physiological discomfort associated with participation are the burden of undergoing a liver biopsy, taking medication, extensive site visits, extra blood samples that will be taken, adverse reactions and serious adverse reactions.

## 1. INTRODUCTION AND RATIONALE

Approximately 400 million individuals worldwide, 6% of the world population, are chronically infected with hepatitis B virus (HBV), and 2 billion have serological evidence of past or present HBV infection.(7)

Worldwide HBV is transmitted mostly perinatally or horizontally early during childhood, whereas in western countries infection is mainly transmitted via sexual intercourse.

Despite the availability of a safe and effective vaccine for more than two decades, HBV infection is still a major global health problem. People with chronic HBV infection are at increased risk of developing hepatic decompensation, liver cirrhosis, and hepatocellular carcinoma (HCC). It is estimated that worldwide 30% of liver cirrhosis and 25% of HCC is due to HBV infection.(8) Mortality estimation models estimated 563,000-1.000,000 deaths due to HBV infection each year, thereby making chronic hepatitis B the seventh leading cause of death in the world. (8-10) Prevalence of chronic HBV infection however is low (0.1-2.0%) in Western Europe and the USA, intermediate in Mediterranean countries and Japan (2.0-8.0%), and high in Southeast Asia and sub-Saharan Africa (8.0-20.0%) (11). The annual incidence of spontaneous HBsAg loss, signifying clearance of the virus, is only 0.1%-0.8% in patients from Southeast Asia, and 1-2% in patients from Western Europe and the USA.

Progression from acute to chronic hepatitis B is influenced by the patient's age at acquisition of the virus. When the virus is acquired perinatally, infection becomes chronic in more than 90% of new borns. In contrast when the infection is acquired during adulthood, most acute individuals clear the infection and only approximately 5% of persons become chronically infected (12).

Figure 1 represents the natural course of chronic hepatitis B, when infection is acquired perinatally. Chronic hepatitis B can present as two distinct forms: HBeAg-positive and HBeAg-negative infection. Patients are rendered for treatment when the patient develops active disease regardless of HBeAg positivity or negativity.

In the last decade therapeutic options for chronic hepatitis B have dramatically improved, which resulted in more patients achieving a state of inactive disease. Unfortunately treatment is not yet optimal, and a cure (i.e. loss of HBsAg) is still far away.

Two types of therapies are currently available for the treatment of chronic hepatitis B:

1) nucleos(t)ide analogues, which are antiviral agents inhibiting the activity of reverse transcriptase, a viral DNA polymerase. Several nucleoside/nucleotide analogues are licensed for the treatment of HBV in the Netherlands; lamivudine, entecavir, telbivudine, which are nucleoside analogues and adefovir dipivoxil (ADF) and tenofovir disoproxil fumarate (TDF),

which are a nucleotide analogues. The mode of action of nucleotide and nucleoside analogues is the same, by inhibiting the HBV reverse transcriptase.(13-16)

## 2) Conventional interferon and pegylated interferon (13, 17, 18).

Interferon alpha has a dual mode of action, with both antiviral and immunomodulatory effects (19-21) and has been recommended as one of the first-line therapies for both HBeAg-positive and HBeAg-negative chronic hepatitis B patients according to the EASL guidelines 2009 (22). Pegylated interferon (Peginterferon alpha2a (Peg-IFN)) is registered for the treatment of HBeAg positive as well as HBeAg negative chronic hepatitis B. Peg-IFN can be administered once weekly due to attachment of interferon alfa-2a to 40 KD branched-chain polyethylene glycol (Peg).

Dutch guidelines advise treatment with anti-virals of all chronic hepatitis B patients with HBV-DNA  $> 2 \times 10^4$  IU/mL with persistent or intermittent elevation of ALT (alanine aminotransferase) above the upper limit of normal (ULN) and with moderate/severe hepatitis on biopsy using a standardized scoring system (e.g. at least grade A2 or stage F2 by METAVIR scoring), regardless if they are HBeAg positive or negative (34).

These types of therapies have suboptimal efficacy. Peg-IFN is administered once weekly subcutaneous and is associated with dose-limiting adverse events. Nucleos(t)ide analogues are better tolerated but require life long administration and therefore nucleoside analogue treatment has been associated with development of drug resistance (23).

For example, the long-term use of lamivudine promotes viral resistance at an estimated rate of 14 to 32% per year. The 5 year resistance for lamivudine is 70%, for adefovir 30%, for entecavir 1.2%, for tenofovir unknown but 0% after 2 years (24). Emergence of resistant mutants or discontinuation of antiviral therapy has been associated with acute exacerbations of liver disease with viral rebound and ALT elevations(13). Although ADF is active against lamivudine resistant mutants, long-term ADF therapy has been found to be associated with development of a, ADF-resistant, rtN236T HBV viral mutation in a small number of patients (25).

In HBeAg-positive patients, HBeAg loss/seroconversion has long been selected as the primary goal of treatment. This is because studies on the natural history of HBV indicate that, in the majority of patients with HBeAg-positive chronic hepatitis B, HBeAg loss/seroconversion (either spontaneous or induced by antiviral therapy) is closely correlated with suppression of HBV DNA, ALT normalization and disease remission (26-28).

Eradication of HBV infection is rendered difficult because stable, long enduring covalently closed circular DNA (cccDNA) and HBV DNA becomes integrated in the hepatocyte nuclei. As the course for chronic hepatitis B into developing cirrhosis/HCC is slow, the major goals of therapy are the long term prevention of progression to irreversible liver damage.

Relatively short-term follow up studies use different surrogate outcomes, which have been proven to be durable and predictive for further progression of the disease. As HBV DNA levels are associated with the progression to irreversible liver damage, the goal of treatment at present has been effective suppression of HBV replication, rather than curing the disease. Recently however, increasing attention is paid to the loss of HBsAg as the primary goal for treatment. HBsAg loss is the most reliable efficacy parameter for both HBeAg-positive and HBeAg-negative chronic hepatitis B. Serum HBsAg is a marker of HBV infection, and antibodies against HBsAg (anti-HBs) signify recovery.

When in current strategies loss of HBsAg and anti-HBs conversion has been achieved, it is considered as the closest outcome to clinical cure of chronic hepatitis B infection. Especially in patients who clear HBsAg before they have developed cirrosis, the prognosis is excellent compared to patients who remain HBsAg positive. Treatment with nucleoside analogues for one year does not increase the loss of HBsAg for both HBeAg positive and negative patients and remains approximately 1%. One year treatment with Peg-IFN results in HBsAg loss of approximately 3% in the HBeAg positive patients and 4% in the HBeAg negative patients. (29). In a study with Peg-IFN and lamivudine therapy for one year with patients with HBeAg positivity, in 11% of patients HBsAg surface loss was seen after 3 years of follow up.

Another long-term follow up study in HBeAg negative patients, treated with Peg-IFN with or without lamivudine for one year showed a 12% loss (both with and without lamivudine) of HBsAg 5 years post-treatment (30).

In our currently ongoing study in patients with a high viral load (HBV DNA  $\geq$  20,000 IU/mL) combination therapy of Peg-IFN and ADF, a rate of 23% HBsAg loss was reported after one year of therapy, which is much higher than currently is observed with other treatment regimens (6). Moreover in this study a positive predictive value of HBsAg loss of 85% was seen when baseline HBsAg levels were less than 675 IU/mL, suggesting that patients with lower baseline HBsAg levels are more susceptible to HBsAg clearance. Treatment in these patients was well tolerated, 4% developed thyroid disease which is comparable to other studies (31). Recent studies have shown that tenofovir is a more potent viral suppressor than adefovir (32). Moreover it has recently been reported that the rate of HBsAg loss in HBeAg positive patients after 2 years of tenofovir (TDF) therapy was 6% (33).

Chronic hepatitis B patients with low viral load (HBV DNA < 20,000 IU/mL) most often have inactive disease and don't require viral suppression according to Dutch guidelines (34). However in the light of the currently highly successful rate of HBsAg loss seen in our ongoing study (6) we hypothesize that a similar rate of HBsAg clearance can be achieved in HBeAg negative patients with low HBV DNA viral load, thereby focusing on cure of the disease rather than viral suppression.

In the light of the suboptimal therapies currently available e.g. the dose limiting adverse reactions of Peg-INF treatment and the development of drug resistance, it is of great practical value to establish predictors of response (or non-response) before or early in the course of anti-viral treatment to assess the success rate of antiviral agents and to guide therapeutic interventions in hepatitis B.

In this study we hypothesize that both treatment with peg-interferon and ADF or Peg-IFN and TDF in HBeAg negative chronic hepatitis B patients with low HBV DNA viral load will induce a high rate of HBsAg loss, comparable to that in patients with high viral load after treatment with ADF and Peg-IFN.

## 2. OBJECTIVES

### 2.1 Primary Objective:

The primary objective is to demonstrate the efficacy of combination therapy (Peg-IFN and adefovir or Peg-IFN and tenofovir) for inducing loss of HBsAg compared to no-treatment in HBeAg negative chronic hepatitis B patients with low viral load. HBsAg loss is defined as HBsAg level < 0.05 IU/mL.

### 2.2. Secondary Objective:

The secondary objectives are to evaluate:

- a. the rate of HBsAg loss and anti-HBs serconversion,
- b. To establish predictive markers at baseline and during the first 12 weeks of treatment for response of primary and secondary endpoints:

serologic markers

HBsAg levels

immunologic markers

T cell responses, cytokine production of T cells.

histologic markers

HAI (histology activity index)

Fibrosis grade

HBsAg level

cccDNA level (liver)

HBV-DNA level (liver)

biochemical markers (livertransaminases)

ALT

AST

LDH

AF

yGT

virologic markers

HBsAg level

cccDNA (plasma)

HBV-DNA level

HDV co-infections

Hostgenomics

DNA and RNA expression levels in PBMC's, liver

Proteomics

Possible protein candidates include: SR-B1(CD36), CD81, certain Claudins, STAT-1 and 2, ApoE and more

Inflammatory markers

CRP, neopterin

Neoplastic markers

Rate of development of hepatocellular carcinoma

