#### **4.4 Sample size calculation**

Per treatment group 44 per group (88 for both groups) is needed to achieve 81% power to detect a difference between the two treatment groups and the control group. The proportion in the Peg-IFN and adefovir group is assumed to be 0.01 under the null hypothesis and 0.20 under the alternative hypothesis. The proportion in the control group (no treatment) is 0.01. The test statistic used is the two-sided Fisher's Exact test. The significance level of the test was targeted at 0.05. A group sample of 44 persons in the control group is needed to achieve a 81% power to detect a difference between the Peg-IFN adefovir or Peg-IFN tenofovir.

Regarding a 10% drop-out due to Peg-IFN side-effects or other reasons a total of 50 patients are needed in each group.

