## 9 STATISTICAL ANALYSIS

### 9.1 Descriptive statistics

The main efficacy variable in the comparison of treatments A and B to treatment C ( no treatment) is the proportion of subjects in each treatment group achieving loss of HBsAg. The primary objective is to demonstrate superior efficacy of treatment A and/or B to treatment C.

The sample sizes were calculated as follows:

Per treatment group 44 per group (88 for both groups) is needed to achieve 81% power to detect a difference between the two treatment groups and the control group. The proportion in the PEG/IFN and adefovir group is assumed to be 0.01 under the null hypothesis and 0.20 under the alternative hypothesis. The proportion in the control group (no treatment) is 0.01. The statistical test used is the two-sided Fisher's Exact test . The significance level of the test was targeted at 0.05. A group sample of 44 persons in the control group is needed to achieve a 81% power to detect a difference between the PEG/IFN adefovir or PEG/IFN tenofovir.

Regarding a 10% drop-out due to peginterferon side-effects or other reasons a total of 50 patients are needed in each group.

Univariate logistic regression analyses will be performed to identify predictors of response to the combination therapy of PEGASYS® and ADF dipivoxil (Hepsera®) and PEGASYS® and tenofovir. Significant predictors from the univariate analysis will be combined into a multivariate logistic regression analysis. As a rule of thumb, the number of potential predictors to be included in a multivariate analysis should not exceed the number of responders (or non-responders, whichever is the lowest) divided by 10. With 100 patients included, the maximum number of predictors in a multivariate analysis is five, assuming a response rate of 0.50. Initially, the number of significant predictors from univariate analysis to be included in the multivariate analysis will be restricted following multi colinearity diagnostics. If the number of potential predictors remains too large however, a bootstrap procedure will be followed drawing 200 samples of the same size as the original (n=100) with replacement, each time repeating the multivariate logistic regression analysis. Descriptives of this bootstrap procedure will be reported to identify a stable predictor set. The level of significance during all these analyses is set at 0.05.

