| HBsAg, anti-HBs (frozen for central processing)                                  | X                    | X                                 | X     | X | X | X | X | X | X  | X  | X  | X  | X  | X  | X               | X                   | X               | X               | X               | X  | X  | X               |
| HBV-DNA (frozen for central processing) i                             | X                    | X                                 | X     | X | X | X | X | X | X  | X  | X  | X  | X  | X  | X               | X                   | X               | X               | X               | X  | X  | X               |
| Alpha-2 macro globulin, Haptoglobin, Apolipoprotein A1                           | X                    |                                   |       |   |   |   |   |   |    |    |    |    |    |    |                 |                     |                 |                 |                 |    |    |                 |
| Viral sequencing                                                                 | X                    | X                                 | X     | X | X | X | X | X | X  | X  | X  | X  | X  | X  | X               | X                   | X               | X               | X               |    |    | X               |

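### HBsAg measured up to week 12 may predict a response defined on the same assay, with no response week and no restriction to patients still HBsAg-positive

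*Protocol*

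**What the plan says.** Section 2.2, item b, sets the aim: "To establish predictive markers at baseline and during the first 12 weeks of treatment for response of primary and secondary endpoints". HBsAg level appears in its marker list under the serologic, histologic and virologic groups. Section 7.1.2 repeats the 12-week window.

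The response is defined on the same analyte in section 2.1: "HBsAg loss is defined as HBsAg level < 0.05 IU/mL". Section 7.1.1 repeats the definition. Section 9.1 names the main efficacy variable as "the proportion of subjects in each treatment group achieving loss of HBsAg". None of these places attaches a week.

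In the Schedule of Assessments, the row beginning "HBsAg, anti-HBs (frozen for central processing" is marked at baseline, day 3, weeks 1, 2, 4, 6, 8 and 12, and every later visit to week 72. Loss can therefore be observed inside the predictor window.

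On method, section 9.1 states: "Univariate logistic regression analyses will be performed to identify predictors of response to the combination therapy". It continues with multivariable selection, collinearity diagnostics and a bootstrap of 200 samples. It has no rule on which patients are still at risk when an on-treatment marker is read.

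**The concern.** A predictor should be read before the event it predicts. Here the marker window overlaps the period in which the event can occur, and for HBsAg the marker and the event are one measurement. A patient below 0.05 IU/mL at week 8 who stays there enters the week-12 model with the lowest possible marker value and with a response already recorded. Such patients create an association even if week-12 HBsAg carries no information for anyone else.

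This matters because the Introduction wants predictors found before or early in treatment so that they can guide therapy. That decision concerns patients still HBsAg-positive. A model driven by patients who have already cleared does not inform it. The bootstrap in section 9.1 would not expose the problem, because resampled data carry the same overlap.

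**Working it through.** **1. The plan's own figures.** Section 4.4 says the treated proportion "is assumed to be 0.01 under the null hypothesis and 0.20 under the alternative hypothesis", with 0.01 in controls, and "The test statistic used is the two-sided Fisher's Exact test". Exact enumeration at 44 per group and alpha 0.05 gives power 0.806, matching the stated 81%. Section 9.1 says: "With 100 patients included, the maximum number of predictors in a multivariate analysis is five, assuming a response rate of 0.50". The sum 100 × 0.50 / 10 = 5 reproduces. Neither figure is in dispute.

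**2. Inputs for the check.**
- Treated patients: 2 × 50 = 100 (section 3).
- Responders: 100 × 0.20 = 20 (section 4.4).
- Number k of the 20 already below 0.05 IU/mL at week 12: not in the protocol, so varied.
- Distribution of week-12 HBsAg among patients still positive, and whether HBsAg is log-transformed: not in the protocol, so varied.

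The marker is given no predictive value among patients still positive, so every significant result beyond the test's own error comes from the overlap.

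**3. Discrimination, without a distributional assumption.** Early clearers rank below all 80 non-responders, and the other responders are at chance:

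AUC = (k/20) × 1 + (1 − k/20) × 0.5 = 0.5 + 0.5 × k/20.

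For k = 0, 1, 2 and 4 this gives 0.500, 0.525, 0.550 and 0.600, so each early clearer adds 0.025. With the 50 responders implied by the 0.50 rate in section 9.1, each would add 0.5/50 = 0.010.

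**4. False-positive rate of the univariate test at 0.05 (simulation).** The logistic rows use a likelihood-ratio test with clearers set at 0.05 IU/mL (log10 = −1.30). A dash means that no figure was computed for that cell.

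| Scale and assumed distribution | k=0 | k=1 | k=2 | k=3 | k=4 |
|---|---|---|---|---|---|
| Logistic, log10, N(3, 0.7) | 5% | 12% | 42% | 78% | 97% |
| Logistic, log10, mean 3, SD 1.0 | – | 11% | 26% | 55% | 83% |
| Logistic, log10, N(2.5, 1.0) | 4% | 10% | 21% | 50% | 75% |
| Logistic, log10, N(2.5, 1.2) | – | 8% | 19% | 37% | 62% |
| Logistic, untransformed IU/mL, from N(3, 0.7) | – | 8% | 9% | 11% | 12–13% |
| Rank test (Mann-Whitney), log10 N(3, 0.8), clearers at 0.04 IU/mL | 4% | 6% | 9% | – | 27% |

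The spread has a simple cause. On the log scale a clearer lies (3 + 1.30)/0.7 = 6.1 SD from the mean under N(3, 0.7), but (2.5 + 1.30)/1.2 = 3.2 SD under N(2.5, 1.2). In untransformed units the low end is compressed and a clearer is barely extreme. A rank test also limits the pull of extreme values, but section 9.1 plans logistic regression.

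**5. Landmark version.** Dropping the k patients already negative and counting only later loss brings the rate back to about 5% on the log scale for every k tried. It leaves 20 − k responders among 100 − k patients.

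**The case against.** The strongest objection is that a protocol names the marker window and the model family, and leaves the analysis set of each secondary model to the statistical analysis plan, which is not shown. A landmark rule may be there. That stands in part: the absence of such a rule alone would not be a finding. But the protocol goes further than silence. It fixes the window, an outcome on the same assay without a date, and a fairly detailed regression procedure. Followed as written, these let the event serve as its own predictor.

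A second objection is that if response means status at week 48 or 72, a week-12 reading does precede the outcome reading, and loss could reverse. This is correct, and it is why the response week has to be stated. It softens the problem without removing it: early clearers who stay negative still make the marker nearly circular.

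A third objection is that nobody may clear by week 12. The Introduction reports 23% loss after one year in the sponsor's high-viral-load study and about 4% after one year of Peg-IFN in HBeAg-negative patients. Neither figure dates loss to the first 12 weeks. This stands in full: with no early clearers there is no artefact.

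A reader might also infer that T-cell, transaminase or RNA markers read after clearance are equally compromised. The protocol gives no basis for that. They are different assays from the outcome, and nothing was calculated for them.

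**Conclusion.** The point holds as a conditional weakness of one secondary analysis. On-treatment HBsAg from day 3 to week 12 can appear predictive when it is uninformative for patients still positive, because some patients may already have met the response definition when the marker is read.

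With 100 treated patients and 20 responders, the false-positive rate is about 5% with no early clearers, about 9% to 42% with two and about 12% to 97% with four. The range reflects the scale on which HBsAg is entered and its assumed mean and SD, none of which the protocol gives. The number of early clearers is also an assumption.

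A reader might infer that on-treatment HBsAg is bound to look predictive, or might take the upper figures as a forecast. The protocol supports neither: the effect needs early clearers, and the high rates need a log scale with a narrow spread. Baseline HBsAg is unaffected because all patients enter HBsAg-positive. The primary comparison with untreated controls is untouched.

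**What to change.** Amend sections 2.2b and 9.1 as follows:
- State the week at which response is assessed.
- For each on-treatment HBsAg model, include only patients still at or above 0.05 IU/mL at that visit.
- Count as response only loss observed after that visit.
- Report separately how many patients had already cleared by then.

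Applying the same landmark to the other on-treatment markers is reasonable for consistency, but the same-measurement argument does not require it. Baseline models need no change.

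The cost is wording, because HBsAg is already scheduled at every visit. The on-treatment models lose the early responders. With four of them, 16 responders remain among 96 patients, and the protocol's own rule of ten gives 16/10 = 1.6 predictors against 20/10 = 2 without the restriction. If nobody clears early, nothing is lost.
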